##### Mental Health Practice Readiness Inventory (MHPRI)

The MHPRI [119] will document practice-level care management competencies shown to predict care uptake [120, 121].

Practice staff will rate each of the 32 items at the practice-level (0 = no function exists; 1 = some function; 2 = function is complete). We will aggregate all informants’ scores to create a total score for practice achievement of care management competencies.

##### Acceptability of Intervention Measure (AIM), Intervention Appropriateness Measure (IAM), and Feasibility of Intervention Measure (FIM)

Secondary implementation outcomes are DOCC acceptability, feasibility, and appropriateness. They will be assessed with three 4-item scales that have excellent internal consistency and good content validity [122].

#### Clinical outcomes

##### Vanderbilt ADHD Diagnostic Rating Scale

Rating scales will be completed by caregivers (VADPRS) and teachers (VADTRS) at each timepoint [123, 124]. Both versions include symptom severity scales as well as performance/impairment items and have excellent psychometrics.

##### Pediatric Quality of Life (PEDS-QL)

Caregivers will complete the PEDS-QL to measure health-related quality of life [125, 126]. It has excellent reliability and treatment validity and is sensitive to DOCC [107].

#### TEAM and LEAD targets and mediators of implementation outcomes

##### Primary Care Team Dynamics Survey (PCTDS)

Staff will complete the 29-item PCTDS to assess affective, behavioral, and cognitive dimensions of team functioning and overall team effectiveness [127]. It has high reliability and discriminant validity [127].

##### Pediatric Integrated Care Survey (PICS)

Caregiver perceptions of team effectiveness will be assessed with the 6-item PICS [128]. The PICS has good reliability, construct validity, and discriminant validity [128].

##### Team Development Measure (TDM)

As a secondary measure of team functioning, staff will complete the TDM, which assesses specific dimensions of team functioning and provides an overall team development score [129]. The TDM has excellent internal consistency and a clear factor structure [129].

##### Implementation Leadership Scale (ILS)

Staff will complete the ILS to capture the extent to which practice leadership is proactive, knowledgeable, supportive, and perseverant toward DOCC implementation [106]. The ILS has strong psychometric properties and contributes to EBP adoption [105, 106, 130–133]. Minor word changes were made to focus the scale on implementation of EPBs for behavioral health in primary care practices.

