#### Professionals

##### Practice leaders

In each practice, we will enroll the lead PCP or medical director (*N* = 24) and practice manager (*N* = 24). Individuals in these positions are responsible for decision-making and management tasks at their sites. Lead PCPs and practice managers in practices randomized to LEAD will participate in Leadership Facilitation.

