##### Primary care providers (PCPs)

We seek to enroll all eligible PCPs at participating practices (*M* = 4.4 PCPs per practice, range: 1–10) to maximize the likelihood that families have an enrolled PCP and enhance generalizability. All PCPs will be provided access to training and encouraged to deliver DOCC. PCPs in practices randomized to TEAM will participate in Team Facilitation.

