**Aim 2: mediators**								
Care team functioning	PCTDS (TDM)	All staff	x		x	x	x	x
Care team integration/quality	PICS	Caregiver	x	x	x	x		
Implementation climate	ICS (ISM)	All staff	x		x	x	x	x
Implementation leadership	ILS (ISM)	All staff	x		x	x	x	x

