##### Implementation Climate Scale (ICS)

Staff will complete the ICS to assess extent to which the practice prioritizes and values implementation of evidence-based practices for behavioral health [104]. The ICS has high reliability and construct validity with organizational measures and is associated with EBP use [77, 104]. As with the ILS, minor word changes were made.

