##### Practice level

We will examine baseline implementation leadership (ILS) and implementation climate (ICS) as moderators of the LEAD condition.

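### Taking the Implementation Leadership Scale from all staff makes the Aim 2 test of LEAD engagement partly a self-rating by the coached leaders

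*Protocol article*

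**What the plan says.** In Table 2, under the Aim 2 mediators, the row for implementation leadership reads "ILS (ISM) All staff" and the row for implementation climate reads "ICS (ISM) All staff", both at months 0, 6, 12, 18 and 24. The Measures section describes the leadership scale thus: "Staff will complete the ILS to capture the extent to which practice leadership is proactive, knowledgeable, supportive, and perseverant toward DOCC implementation". For the climate scale it says: "Staff will complete the ICS to assess extent to which the practice prioritizes and values implementation of evidence-based practices for behavioral health".

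Under Practice leaders, in each practice "we will enroll the lead PCP or medical director", together with the practice manager, 24 of each. The same section adds: "Lead PCPs and practice managers in practices randomized to LEAD will participate in Leadership Facilitation". The other enrolled professionals are the PCPs (mean 4.4 per practice, range 1–10) and one care manager (CM) per practice.

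Under Statistical analyses, Aim 2, gains in implementation leadership and climate are the engagement hypothesis for LEAD, and the two constructs are then tested as mediators of LEAD. Under Randomization, practices learn their condition once baseline data are in.

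**The concern.** The leadership scale asks how well practice leadership supports DOCC implementation. For the lead PCP and practice manager this is a rating of themselves. Leaders rate themselves in all four conditions, but only in the LEAD and TEAM + LEAD practices have they been coached to lead this implementation, and they know it. Any change in self-rating that comes from the coaching itself therefore differs by arm and does not cancel in the comparison.

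What is at stake is the reading of a positive engagement result. If the practice score pools all raters, a gain in LEAD practices could mean that staff see better leadership, or only that coached leaders rate themselves higher. The trial sets out to separate the mechanisms of the two strategies, so the distinction matters. The TEAM targets include one outside informant, the caregiver-rated integration survey (PICS). The LEAD targets have none, and the secondary inner-setting scales are also completed by staff.

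**Working it through.** The plan states no power or error figure for this point, so there is nothing to reproduce. The check has four steps.

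**1. Are leaders among the raters?** Table 2 uses narrower labels where it means them: the manager for the practice information survey and the CM for the staff information form. The sections on assessments, on the ILS and on the ICS exclude nobody. All staff is not defined in words, so inclusion is an inference, but every textual cue supports it.

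**2. Share of raters who are leaders.** There are two leaders and one CM per practice. If the lead PCP is counted among the PCPs, raters = PCPs + 2. If the lead PCP is additional, raters = PCPs + 3.

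| PCPs | Lead PCP within count | Lead PCP additional |
|---|---|---|
| 1 | 2/3 = 67% | 2/4 = 50% |
| 4.4 (mean) | 2/6.4 = 31% | 2/7.4 = 27% |
| 10 | 2/12 = 17% | 2/13 = 15% |

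**3. Shift in the practice score if only leaders' ratings move.** With equal weight per rater, n raters and a leader-only shift d in rater SD:

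shift in practice-level SD = (2/n) × d / √(ICC + (1 − ICC)/n)

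The values of d (0.5–0.8) and of the ICC (0.1–0.3) are assumptions.

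- Upper end, n = 6.4, d = 0.8, ICC 0.1: 0.3125 × 0.8 / √(0.1 + 0.9/6.4) = 0.250 / 0.491 = 0.51.
- Lower end, n = 7.4, d = 0.5, ICC 0.3: 0.270 × 0.5 / √(0.3 + 0.7/7.4) = 0.135 / 0.628 = 0.22.
- At d = 0 the shift is 0. A negative d would bias the score downwards by the same formula.

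**4. Effect on the engagement test.** A simulation of 20,000 trials compared 12 LEAD with 12 non-LEAD practices. Each practice had six raters (two leaders, four others), non-leaders saw no change, and practice means were compared by a two-sided t-test at 5%. The test was of scores at one time point, a simplification of the planned longitudinal model.

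| Leader-only shift (rater SD) | False positives, ICC 0.1 | False positives, ICC 0.3 |
|---|---|---|
| 0 | 4.9% | 4.9% |
| 0.5 | 11.9% | 9.4% |
| 0.8 | 23.3% | 16.2% |
| 1.0 | 34.3% | 22.5% |

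Here a false positive means a significant result when no non-leader perceives any change. With leader ratings left out, the rate was 4.7–5.3% in every setting.

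**The case against.** The strongest objection is that the article says who completes the scale, not how it is scored. The only stated aggregation rule, pooling all informants, is for the practice readiness inventory (MHPRI). Collecting from all staff is compatible with scoring non-leaders only, and a SAP could say so. This stands as a limit: a reader might infer that the plan commits to putting leaders' ratings into the ILS practice score, and it does not say that. But the rater source is stated, no separation by role is mentioned, and using that source as it stands inflates LEAD engagement whenever coaching raises self-ratings.

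Three wider readings are tempting and not supported:

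- *The climate score is also a self-rating.* The ICS asks about the practice. Leaders rate it as the treated party, which is a weaker problem.
- *The Aim 3 moderators are contaminated.* The plan says "We will examine baseline implementation leadership (ILS) and implementation climate (ICS) as moderators of the LEAD condition", but baseline ratings are collected before practices learn their allocation, so coaching cannot have shifted them.
- *The mediated effect would be spurious.* A leader-only shift biases the path from LEAD to the mediator. It does not by itself create a path from mediator to outcome, and the primary outcome comes from provider service logs.

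On size, the leader-only shift is assumed. Even at 0.22–0.51 SD, a 12 versus 12 comparison would reach significance only about 8–22% of the time. The effect detectable with 80% power there is about 1.2 SD.

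Finally, staff who are themselves treated also rate the TEAM target, and the proposed non-leader raters are themselves facilitated in TEAM + LEAD practices. Both are true, and excluding leaders does not give blinded raters. It does remove the people whose own conduct the ILS scores.

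**Conclusion.** The concern holds for one test: LEAD engagement on the ILS, which is also the LEAD-to-mediator path. On the most natural reading of Table 2, coached and unblinded leaders supply roughly 27–31% of the ratings of their own leadership at the mean practice, and 50–67% in a one-PCP practice. Those shares assume that all enrolled staff respond and count equally.

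The resulting bias cannot be sized from the documents. It runs from 0 with no leader-only shift to about 0.22–0.51 practice-level SD under the assumed shifts of 0.5–0.8 rater SD and ICC of 0.1–0.3. The ICS deserves a check by rater role and no more. The Aim 3 baseline moderators, the primary outcome and the Aim 1 effects of LEAD on it are not affected.

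**What to change.** State before analysis that, for the Aim 2 LEAD engagement and mediation analyses, the main ILS practice score is formed from non-leader raters: the PCPs other than the lead, and the CM. Report leaders' self-ratings separately, and keep the all-rater score as a sensitivity analysis. For the ICS, keep the all-staff score and report results by rater role (leader versus non-leader) as a sensitivity analysis. Leave the Aim 3 moderator scores as they are.

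This needs wording only and no new data. The cost is precision. The reliability of a mean of k raters is k × ICC / (1 + (k − 1) × ICC). Going from 6.4 to 4.4 raters lowers it from 0.64/1.54 = 0.42 to 0.44/1.34 = 0.33 at ICC 0.1, and from 1.92/2.62 = 0.73 to 1.32/2.02 = 0.65 at ICC 0.3. Where a practice's only PCP is its lead, the CM is the sole remaining rater and reliability equals the ICC itself, 0.1–0.3. Such practices should be flagged in the report. The report should also say that non-leader raters in TEAM + LEAD practices are themselves facilitated.

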##### Implementation Climate Scale (ICS)

Staff will complete the ICS to assess extent to which the practice prioritizes and values implementation of evidence-based practices for behavioral health [104]. The ICS has high reliability and construct validity with organizational measures and is associated with EBP use [77, 104]. As with the ILS, minor word changes were made.

##### Inner Setting Measures (ISM)

As secondary measures, staff will complete three scales assessing overall culture, implementation climate for DOCC specifically, and leadership engagement. These scales have good factor structure, internal consistency, and discriminant validity [134].

#### Potential moderators of the effects of TEAM or LEAD on implementation outcomes

##### Team/provider level

We will test whether negative staff attitudes about BH services (Physician Belief Scale (PBS)) [135] or the CM’s discipline (nursing vs. mental health; SIF) at baseline moderates the effects of TEAM.

##### Practice level

We will examine baseline implementation leadership (ILS) and implementation climate (ICS) as moderators of the LEAD condition.

##### Family level

We will test three family characteristics as moderators of TEAM or LEAD (i.e., caregiver gender, caregiver race/ethnicity, child baseline ADHD severity).

#### Fidelity

##### Fidelity to implementation condition

We will follow Proctor et al.’s recommendations for specifying and reporting implementation strategies [136] and develop implementation manuals for both TEAM and LEAD describing key steps and activities (see Supplemental File 3). Facilitators will track attendance, participation, and activities completed during facilitation calls. They will also record specific barriers, solutions, and next steps.

##### Fidelity to DOCC

Fidelity to DOCC will be documented in two ways. First, we will evaluate dosage for all cases. We define adequate dosage as at least 6 DOCC encounters and at least 1 care management meeting for each case [137, 138]. Second, we will assess fidelity by reviewing audio recordings of DOCC treatment sessions. CMs will upload two session audio recordings for cases that consent to recording via a secure, HIPAA-compliant audio portal. A trained research assistant (unaware of implementation condition) will rate recordings using the Treatment Integrity Rating Form [139].

### Power and sample size

Our power calculations for Aim 1 are based on comparisons of provider and patient outcomes among the six practices in each of the four conditions in the factorial design. For our primary implementation outcome (number of DOCC sessions), we estimate 80% power to detect an effect size (ES) of 0.42. Given our modest practice sample size, we will explore group differences in practice-level CCM core competencies. In our prior trial, large ESs were found for provider changes in behavior management practices (*ES* = 0.78) and perceived competencies (*ES* = 0.77) [107]. For patient outcomes, we assume an ICC of 0.01 in cases treated by the same provider and 20% attrition based on prior work [107, 109]. In a simple RCT with 262 cases/condition, we can detect an effect size as small as 0.25. The effect size for clinical improvement in individualized targets in our prior trial was 0.60, indicating that our sample size provides adequate power to detect group differences in patient outcomes [107].

Power calculations for mediator analyses (Aim 2) are based on simulation studies [140]. Because the sample sizes per cell are modest (6 sites per condition), we are powered to detect large effects. This seems justifiable insofar as smaller effect sizes (e.g., 0.35–0.50) are of less interest given the higher cost of using more intensive combined implementation strategies. Thus, our mediational tests are powered only for a large effect size. For our moderator analyses (Aim 3), we have power 0.80 to detect small effects of *f-square* = 0.03.

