### The EBP: DOCC

Doctor–Office Collaborative Care (DOCC) is a cross-diagnosis intervention for treating DBDs and comorbid ADHD in community pediatric practices [107–109]. DOCC is based on the CCM’s core components adapted for the medical home [11, 12, 50, 110]. In randomized clinical trials, DOCC improved service access (99% vs. 46%) and completion (77% vs. 12%), personalized behavioral and ADHD targets, externalizing and ADHD symptoms, remission rates, family satisfaction, and provider self-efficacy and effectiveness, with most symptom resolution in fewer than 11 contacts [107–109, 111]. We also documented lower BH care costs at 12-month follow-up for DOCC [112].

In this trial, the DOCC package includes an implementation guide and a provider treatment manual. The implementation guide includes resources and guidelines for key care management processes that support the six CCM principles: organizational support, delivery system redesign (e.g., team roles, workflows), clinical decision support (e.g., use of standardized rating scales), clinical information systems (e.g., patient registry), self-management support (e.g., workbook), and community resources. The treatment manual includes DBD modules with skills for caregivers and children (e.g., anger management, parenting) and ADHD modules that address psychoeducation, shared decision-making, and medication recommendations. The care team is responsible for assessing treatment progress, individualizing session frequency and treatment dose, and coordinating with other services.

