#### Standard REP (no facilitation)

All practices will receive DOCC manuals and training and participate in the same study initiation meetings (e.g., staff introductions, orientation to study procedures). Each provider will receive access to DOCC virtual training, which includes content and care processes organized into nine clinical topics, each with brief videos and post-training knowledge quizzes. Providers can use the platform to contact study staff for technical assistance and clarification or discussion of training content. The training platform will record data on progress, completion, and performance (e.g., modules accessed, quiz scores), and providers will receive continuing education credits. All sites will receive ongoing technical assistance during the implementation phase.

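### The claim of adequate power for patient outcomes rests on an effect size of 0.60 from a trial of DOCC itself, on an outcome not listed here, although all four conditions receive DOCC

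*Protocol article*

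**What the plan says.** For patient outcomes, the Power and sample size section first sets out its assumptions: "we assume an ICC of 0.01 in cases treated by the same provider and 20% attrition based on prior work". It then gives a detectable effect: "In a simple RCT with 262 cases/condition, we can detect an effect size as small as 0.25". Finally it brings in a benchmark and draws its conclusion from it: "The effect size for clinical improvement in individualized targets in our prior trial was 0.60, indicating that our sample size provides adequate power". The sentence applies that conclusion to group differences in patient outcomes. The benchmark is cited to reference 107.

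Other sections show what is compared here:

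- **Treatment given.** Standard REP (no facilitation) states: "All practices will receive DOCC manuals and training". Study design says that care teams deliver DOCC to the enrolled children.
- **Contrast tested.** Statistical analyses, Aim 1, tests TEAM, LEAD and their interaction relative to REP only, for symptom severity and quality of life.
- **Measures.** The Abstract, Table 2 and the Clinical outcomes section list VADPRS, VADTRS and PEDS-QL. None lists individualized targets.
- **Source of the benchmark.** The EBP: DOCC section cites reference 107 among the randomized trials of DOCC. The PEDS-QL section cites the same reference for sensitivity to DOCC.

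**The concern.** A power claim holds for a particular contrast on a particular outcome, and the 0.60 matches neither. It describes clinical improvement in a trial of DOCC. Here the randomized difference is facilitation added to a DOCC programme that all practices receive, so facilitation can reach a child only through more DOCC or better DOCC. An effect of DOCC is not an effect of facilitating DOCC.

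The outcome differs too. Individualized targets are chosen for the child, and an effect size on them need not carry over to a fixed symptom scale or a quality-of-life scale.

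What is at stake is how a null clinical comparison would be read. The article hypothesizes significant improvement in child symptoms and quality of life, and it asserts adequate power for group differences. A reader who accepts that assertion may take a null as evidence that facilitation does not help children.

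**Working it through.** **Inputs from the article.** Benchmark 0.60. Detectable effect 0.25 with 262 cases per condition. ICC 0.01 for cases treated by the same provider. Attrition 20%. Up to 25 caregivers in each of 24 practices, at most 600. Six practices per condition. A mean of 4.4 PCPs per practice.

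**Assumptions.** Alpha is not stated; I take 0.05 two-sided. The 80% power is stated for the primary outcome; I carry it over to patient outcomes. For the available-case figures I apply ICC 0.01 at practice level.

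**1. The article's own figure.** n per arm = 2(1.960 + 0.842)² / 0.25² = about 251 (252 with the t correction). About five cases per provider (25/4.4 = 5.7 at full enrolment) gives a design effect of 1 + (5 − 1) × 0.01 = 1.04, and 252 × 1.04 = 262. The 0.25 reproduces, so the arithmetic of that sentence is sound.

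**2. The cases available.** 600/4 = 150 per condition and 600/2 = 300 per factor level. After 20% attrition these are 120 and 240. By comparison, 262 in each of four conditions would be 4 × 262 = 1,048.

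**3. Detectable effects with those cases.** Retained cases per practice: 25 × 0.8 = 20. Design effect: 1 + (20 − 1) × 0.01 = 1.19. The detectable effect is multiplier × √(2/n_eff). The multiplier is 2.80 on the normal scale. With 24 − 4 = 20 between-practice degrees of freedom it is 2.086 + 0.860 = 2.946.

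| Contrast | n per side | n_eff = n/1.19 | √(2/n_eff) | Normal | 20 df |
|---|---|---|---|---|---|
| Main effect of TEAM or LEAD | 240 | 201.7 | 0.0996 | 0.28 | 0.29 |
| One condition v REP only | 120 | 100.8 | 0.1408 | 0.39 | 0.41 (0.415) |

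**4. How far adequacy depends on the presumed effect.** These effects are for illustration only (normal approximation). The article gives no expected effect of facilitation on children.

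| True effect | 262 per condition, no clustering | Main effect, 240 v 240 | One condition v REP only, 120 v 120 |
|---|---|---|---|
| 0.20 | 0.63 | 0.52 | 0.30 |
| 0.30 | 0.93 | 0.85 | 0.57 |
| 0.60 | >0.99 | >0.99 | 0.99 |

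With 20 df the main-effect entries at 0.20 and 0.30 become 0.48 and 0.82. At 0.60 every contrast is well powered. At one third of 0.60 none reaches 80%, even with the stated 262. So the word adequate is carried by the choice of 0.60.

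**The case against.** The best defence is that the article gives the detectable effect of 0.25 immediately before the benchmark, so a reader can judge power without the 0.60. The clinical outcomes are already labelled secondary, in a hybrid type 3 trial whose primary outcome is DOCC encounters. No sample size or decision rule hangs on the sentence. The comparator behind 0.60 is not stated. The article also says that REP alone is unlikely to suffice in many lower-resourced settings; if REP-only practices delivered almost no DOCC, the contrast could come close to DOCC against none. Finally, Table 2 is headed as primary constructs in a condensed article, and the earlier trials did report gains in externalizing and ADHD symptoms.

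Much of this stands. It limits the point to the inference and leaves the 0.25 intact. It does not rescue the inference: near-absent DOCC under REP only would make 0.60 a best case, not a planning value, and the article itself expects that REP may be enough for some sites.

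A reader might go further and scale 0.60 by the reported completion difference (77% against 12%) to infer an expected effect of roughly 0.1 to 0.3. The documents do not support this. The completion figures are cited to several trials together, while 0.60 is cited to one. Linearity in completion is an outside model. TEAM also targets skill and fidelity, which could change the benefit per session as well as the number of sessions.

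**Conclusion.** The statement that the sample size gives adequate power for patient outcomes is unsupported, because its benchmark belongs to another contrast and to an outcome not listed among the clinical measures. With the cases available, the design detects about 0.28 to 0.29 for a main effect and about 0.39 to 0.42 for one condition against REP only. These figures rest on two-sided alpha 0.05, 80% power, full enrolment of 600, 20% attrition, and ICC 0.01 moved from provider to practice level; a larger practice ICC would raise them.

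A reader might infer that the trial is underpowered for children's outcomes. That is not shown either: a facilitation effect of 0.30 would have about 0.85 power as a main effect (0.82 with 20 df), and one of 0.20 about 0.5. The true size is unknown, though probably below the DOCC effect. The finding concerns a claim to be restated, not a fault in the design.

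**What to change.** In Power and sample size:

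1. Delete the sentence that infers adequate power from 0.60.
2. State the detectable effects for the contrasts actually tested with the cases available, together with alpha, power, attrition, and the ICC and the level at which it applies. Under the assumptions above these are about 0.28 to 0.29 (240 v 240) and about 0.39 to 0.42 (120 v 120).
3. Say that all conditions receive DOCC, and that the effect of facilitation on children is unknown and probably smaller than that of DOCC itself.
4. Say that the secondary clinical results will be reported as estimates with confidence intervals, and that a null will not be read as absence of benefit.

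Do not insert an expected effect of 0.1 to 0.3; that would replace one unsupported benchmark with another. The cost is a few sentences and a less favourable power statement. Design, sample size and analysis do not change.
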